#### Moderating Variables

Social support will be measured using two subscales (positive interactions and emotional and informational support) of the Medical Outcomes Study Social Support Survey [44], a multidimensional instrument that is valid in Chinese-speaking patients [45]. Each item is rated on a 5-point scale (1=none of the time, 2=a little of the time, 3=some of the time, 4=most of the time, 5=all of the time). The summed subscale scores include eight items for emotional and informational support and four items for positive interactions. The overall scale score is the sum of the two subscales, with higher scores indicating greater social support.

Dispositional optimism will be assessed using the Chinese Revised Life Orientation Test [46], which comprises three positively worded (eg, “I am always optimistic about my future”) and three negatively worded (eg, “I hardly ever expect things to go my way”) phrases. Each item is rated on a 4-point scale (1=disagree, 2=neutral, 3=agree, and 4=strongly agree). Higher summed scores indicate higher optimism.

Perceived control of illness will be measured using three items previously used in a psychosocial intervention with breast cancer survivors [15]. These items assess perceived control of the future course of illness, day-to-day symptoms, and emotions related to illness, with each rated on a 4-point scale (0=none, 1=a little bit, 2=somewhat, and 3=a lot). Higher scores on the summed items indicate greater perceived control.

The FACT-B, CES-D, Self-Stigma Scale, Chinese Revised Life Orientation Test, Perceived Stress Scale, and Medical Outcomes Study Social Support Survey have been validated in Chinese populations, and the other scales have been or will be translated into Chinese and back-translated into English by bilingual researchers through an iterative process to ensure conceptual and linguistic equivalence. Most of the Chinese versions have been used in previous studies [47] and have demonstrated good psychometric properties and psychometric equivalence to the original English versions (Cronbach α=.83-.98).

#### Qualitative Data

A subsample of patients (n=77) will participate in focus groups or individual semistructured interviews. Seven focus group interviews (n=35) will be conducted among the Joy Luck Academy participants to identify common themes surrounding their Joy Luck Academy experience. Approximately 4 to 6 respondents from each Joy Luck Academy cohort will be approached by the program facilitator to participate in the focus groups [48]. The focus groups will be conducted within 1 week of completion of the intervention. The community research coordinator, who has been trained in qualitative interviewing, will conduct the focus group interviews at the HCA.

Individual interviews will be conducted after the last follow-up assessment to explore the culturally specific mechanisms that may explain the potential intervention effect. In-depth semistructured individual interviews will be conducted with 42 participants (half from the control group and half from those in the intervention group who have not participated in the focus groups). Approximately 6 women from each Joy Luck Academy cohort will participate in individual interviews to reach data saturation [49]. Each interview will last 60 to 90 minutes. These interviews were designed to explore participants’ breast cancer experience, cancer management, supporting resources, concerns, and the effect of cancer on their lives and social networks. Each topic area will be evaluated to identify additional information and specific examples. Joy Luck Academy participants will also be asked about their experiences in the Joy Luck Academy and the changes they had experienced as a result of the Joy Luck Academy. The inductively and deductively designed interview topic guide was finalized through discussion with the HCA. Permission to audio record the individual interviews and focus groups will be obtained from the participants. Participants will receive an additional US $30 compensation for the interviews.

### Data Analysis

#### Deductive Data Analysis Plan

Descriptive statistics and correlations among the major variables will be computed. The internal consistency of the questionnaires’ reliability at baseline will be assessed using Stata 16.0 software (StataCorp LLC). The construct validity of the questionnaires will be assessed using confirmatory factor analysis with Stata 16.0. Appropriate techniques (eg, exploratory factor analysis) will be used to improve reliability and validity, when necessary.

The primary analytic strategy will be multilevel analyses, also referred to as hierarchical linear modeling or linear mixed-effects modeling. Specifically, for each outcome variable, the primary independent variables of interest will include the intervention condition (experimental vs control), time (postintervention and 1- and 4-month follow-ups), and the interaction between the intervention condition and time. Random subject or Joy Luck Academy cohort effects, as applicable, will be used to model the correlations between repeated measurements within subjects and between observations from subjects within Joy Luck Academy cohorts. The selection of the random-effect covariance and serial correlation structure (eg, autoregressive correlation), as appropriate, will be based on the Bayesian information criterion. Each hierarchical linear modeling for assessing aim 1 will use quality of life as the primary outcome and other specified variables as secondary outcomes, controlling for the baseline outcome. In addition, results will be reported by controlling for important covariates used in the randomization (eg, age at baseline, cancer stage, and time since treatment) [50]. We will analyze the impact of the intervention on cortisol by testing the change in diurnal profile from pre- to postintervention using linear mixed-effects modeling. Cortisol outcomes will be indicated by raw cortisol values, initial levels, slopes, and areas under the curve, following previous methods [51-54].

Moderation effects (aim 2) will be assessed by adding potential moderators and testing their interactions with the intervention condition and time, one moderator at a time, and testing the significance of the interaction effect between the moderator and the intervention (and time, as appropriate). Mediation effects (aim 3) will be assessed by examining bootstrapped 95% CI of the indirect effect of the intervention on the primary and secondary outcomes via each hypothesized mediator [55,56]. In the presence of more than one significant single mediator, we will fit multiple mediator models to evaluate the joint mediation effects of multiple mediators [55,57]. All statistical tests will be conducted at a two-sided significance level of *P*=.05. Except for the primary analysis for the quality-of-life outcome, the findings based on other analyses will be interpreted with caution because of a lack of control over the overall type 1 error rate across multiple tests. Effect sizes with 95% CIs will also be calculated for models to help characterize the magnitude and potential replicability of the findings.

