### Power Analysis

Power analysis was based on the primary aim of this trial. Specifically, we calculated the sample size required to detect the effect of Joy Luck Academy on the primary outcome (quality of life at the 4-month follow-up assessment). In our primary analyses, we will use maximum likelihood-type (eg, restricted maximum likelihood) estimation procedures based on all observed data, assuming a missing-at-random mechanism [25]. The pilot study revealed that the Joy Luck Academy had an intermediate or higher effect on improving participants’ quality of life (Cohen *d*=0.47), depressive symptoms (Cohen *d*=0.55), and positive affect (Cohen *d*=0.62). On the basis of a targeted medium effect size of Cohen *d*=0.47, we estimated that a total sample size of 146 women at the 4-month follow-up would yield 80% power to detect this treatment effect at α=.05 (nQuery Advisor Version 7.0, Statistical Solutions Ltd). Assuming an attrition rate of 10%-20%, the final recruitment goal will range between 162 and 183 at the baseline.

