Each peer mentor will work with 3 to 5 mentees. Peer mentors will lead small group discussions on that week’s topic and share their own experiences with mentees. This setup will encourage and allow mentees to share personal feelings in a relaxed and comfortable setting and receive support and advice. Mentors will also contact mentees once a week during the 7-week program to provide guidance and address remaining concerns. Each participant will be assigned to a volunteer peer mentor who is a breast cancer survivor and speaks a similar Chinese dialect. Mentors will be recruited from graduates of Joy Luck Academy pilot programs. Each potential mentor will be evaluated by the program facilitator based on the potential mentor’s engagement in the program and support of other participants during the program. Mentors will complete a 3-hour training program to gain mentoring skills. The training will be conducted by HCA staff using a standardized manual that was jointly developed by the academic and community teams. The training program focuses on skills in establishing rapport, demonstrating understanding, listening empathically, discussing participants’ concerns, and promoting the sharing of information and feelings. The training also involves lectures, case study presentations, discussions, and role-play activities.

We will use a procedure to maximize attendance and retention recommended by a previous study [27]. Participants will be asked to notify the program facilitator or their assigned mentor in advance if they will be absent. They will be told that, with their permission, the group members will be informed of the reason for their absence to reduce worries and concerns. The mentor will keep copies of the handouts for missing participants and call them within 5 days to briefly discuss the week’s topic and tell them that they can pick up the handouts when they return to class. This should make participants feel that they are cared for by others and that they can catch up and will make them more likely to continue the program. Participants will also be informed that the lectures, recorded in DVD format, will be available for them to view at home so that they will not miss information in the lecture.

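### Clustering arises in the intervention arm only, but the protocol leaves the cohort effect optional, does not confine it to that arm, and omits it from the power calculation

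*Protocol article*

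**What the plan says.** Women are randomised individually, about 1:1 (Randomization). Intervention women attend one of seven programs, each a weekly class over seven weeks with group sharing, and "Each peer mentor will work with 3 to 5 mentees" (Intervention Group). Control women are told to read booklets by themselves (Control Group).

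For the model, the Deductive Data Analysis Plan states that "Random subject or Joy Luck Academy cohort effects, as applicable, will be used to model the correlations", and goes on to name correlation between repeated measurements in a woman and between women in the same cohort. The next sentence says that the choice of random-effect covariance and serial correlation structure, "as appropriate, will be based on the Bayesian information criterion". It does not say whether the cohort effect applies to both arms.

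The Power Analysis section states: "On the basis of a targeted medium effect size of Cohen *d*=0.47", "a total sample size of 146 women at the 4-month follow-up would yield 80% power to detect this treatment effect". It gives no ICC, group size or design effect.

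**The concern.** Group sharing and peer support are part of the treatment, so outcomes among women in the same class may be correlated in a way that has no counterpart among controls. The standard error of the arm difference is then right only if the model carries a class-group variance for the intervention arm. The wording allows two models that do not: one with a subject effect only, and one with a cohort intercept common to both arms, which largely cancels from the arm comparison.

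The test at stake is the quality-of-life comparison. It is the one analysis that the protocol exempts from its caution about uncontrolled type I error. The stated 80% power also takes no account of a correlation that the analysis section itself expects.

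**Working it through.** **1. The plan's own figure.** Inputs are d = 0.47, α = 0.05 and 80% power (Power Analysis), two-sided ("All statistical tests will be conducted at a two-sided significance level of" .05, Deductive Data Analysis Plan). For an independent two-sample t test, 72 per arm gives power 0.7998 and 73 per arm gives 0.805, so N = 146. The attrition range also follows: 146/0.9 = 162.2 and 146/0.8 = 182.5, against the stated 162 to 183. The calculation contains no allowance for clustering.

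**2. Group size.** With 168 women, 1:1 allocation and seven programs, 84/7 = 12 women per class at entry. With 73 evaluable, m = 73/7 = 10.4. The stated 24 per program is a maximum.

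**3. One-arm clustering, no baseline adjustment.** The SD is 1 and the ICC is an assumption, since the document gives none.

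- Design effect in the intervention arm: DE = 1 + (m − 1) × ICC.
- Variance of the difference: V = DE/73 + 1/73, against 2/73 under independence.
- Ratio of true to independence SE: √[(DE + 1)/2].
- Type I error if clustering is ignored: 2[1 − Φ(1.96/ratio)].
- Power, normal approximation: Φ(0.47/√V − 1.96).
- Satterthwaite df: (DE + 1)²/(DE²/6 + 1/72).

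Example at ICC 0.05: DE = 1 + 9.43 × 0.05 = 1.471; V = 2.471/73 = 0.0339; SE = 0.184 against 0.1655; ratio 1.112; type I error 7.8%; power Φ(2.554 − 1.96) = 72%; df = 6.107/(0.361 + 0.014) = 16.3.

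| ICC | DE | SE ratio | Type I error if ignored | Power, normal | Power, Satterthwaite (df) |
|---|---|---|---|---|---|
| 0.01 | 1.094 | 1.02 | 5.5% | 79% | 75% (20.5) |
| 0.02 | 1.189 | 1.05 | 6.1% | 77% | 73% (19.2) |
| 0.05 | 1.471 | 1.11 | 7.8% | 72% | 67% (16.3) |
| 0.10 | 1.943 | 1.21 | 10.6% | 65% | 58% (13.5) |

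At ICC 0 the normal approximation gives 81% and the t test 80.5%.

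**4. Does a shared cohort intercept help?** In wave j the intervention mean carries c_j + u_j and the control mean carries c_j, where u_j comes from the class. The difference leaves u_j, while a shared intercept models only c_j. A simulation (20,000 trials per setting, seven classes of 10 or 11, intervention-only clustering, 4-month outcome alone) gives these type I errors at ICC 0.05 and 0.10:

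- no cohort effect: 8.0% and 10.7%;
- shared intercept: 8.2% and 11.2%;
- intervention-only effect, tested on 144 df: 5.6% and 6.1%.

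At ICC 0.05 the mean reported SE is 0.163 (none) or 0.161 (shared), against a true SE of 0.182. A further simulation with classes of 10 gave 6.4%, 8.0% and 10.7% for the shared intercept at ICC 0.02, 0.05 and 0.10, and about 5% with an intervention-only effect.

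**5. If BIC decided whether the term stays.** In the first simulation BIC kept a true intervention-only effect in 5.5% of trials at ICC 0.05 and 18% at ICC 0.10. Type I error after selection was 7.6% and 9.1%.

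**6. Baseline adjustment.** Assume a baseline correlation of 0.6, so the outcome variance falls to 1 − 0.36 = 0.64, and hold the group variance fixed. At ICC 0.05, V = 2 × 0.64/73 + 0.05 × (1/7 − 1/73) = 0.01753 + 0.00646 = 0.0240. Power is about 86% (81% with Satterthwaite df). At ICC 0.10, V = 0.01753 + 0.01292 = 0.0305, and power is about 77% (69%). Adjustment does not cure the SE error: at ICC 0.05 the ratio becomes √(0.0240/0.01753) = 1.17.

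**7. What is a cohort?** Under Qualitative Data, "Approximately 6 women from each Joy Luck Academy cohort will participate in individual interviews"; 7 × 6 = 42, the stated number of interviews, and half are with controls. That cohort contains both arms. The Randomization section also ties assignment of both arms to the start of each cohort. The focus-group sentence under Qualitative Data, however, draws 4 to 6 respondents per cohort from attendees only. Usage is mixed.

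**The case against.** The strongest reply is that the plan names the very clustering it is said to neglect. It can be read as using each random effect for its own purpose: subject effects for repeated measures, cohort effects for women in the same program. If cohort there means attendees, the effect is already confined to the intervention arm. The BIC sentence most naturally concerns the form of the covariance, not whether a level is kept. The same instructors, lectures and materials across programs limit one source of between-class variance. The planned adjustment for baseline may bring power back above 80%. Details such as the degrees-of-freedom method are usually left to a fuller plan.

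Much of this stands. A reader might infer that the protocol specifies a cohort effect shared by both arms. It does not: the analysis section is silent, and the other sections use the word both ways. A reader might also infer that BIC will remove the term; that is one possible reading only.

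What the reply does not remove is that a rule is stated, it makes the term optional, and it admits models that give a wrong standard error for the primary test. That goes beyond missing detail.

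**Conclusion.** The point holds in conditional form. If the ICC is above zero and the class effect is omitted or shared across arms, the true primary standard error exceeds the reported one by about 2%, 5%, 11% or 21% at ICC 0.01, 0.02, 0.05 or 0.10. Type I error is then about 6%, 8% and 10-11% at 0.02, 0.05 and 0.10. These figures assume seven classes of about 10 evaluable women and equal variances; the ICC values are assumptions.

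The 146 and 80% make no allowance for clustering. It does not follow that the trial is underpowered: the loss to 77%, 72% or 65% (lower with small-sample df) applies without baseline adjustment, and whether adjustment offsets it depends on two inputs that the document does not give. Nor can one say outright that the primary standard error is too small: at ICC 0, or with an effect confined to the intervention arm, the problem disappears or nearly so.

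**What to change.** State that the primary model includes, besides the within-woman correlation, a random class-group effect for intervention women only, with each control woman as her own singleton. Keep it whatever its estimate or BIC value, and use Satterthwaite or Kenward-Roger degrees of freedom to reflect seven groups. Define cohort once, saying whether it includes controls. A shared wave intercept may stand beside the class effect but cannot replace it. This point needs no change to the covariance across visits.

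Restate the power for 146 women over a range of ICC and baseline correlation. Data collection ended in February 2019, so this informs interpretation and calls for no further enrolment.

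The cost is a few lines of wording and a somewhat wider confidence interval, with few degrees of freedom for the class variance.

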### Randomization

Participants who consent to participate will be randomly assigned to the Joy Luck Academy or control group at an approximate 1:1 ratio. Using minimization—a covariate adaptive randomization approach [26]—we will assign a participant to the intervention or control group by applying a randomization algorithm that will take into account participants’ age, stage of cancer, and time since completing treatment. This covariate information will be obtained by the HCA staff during the participant screening process. Randomization will start 4 weeks before the orientation scheduled start date and continue until the recruitment goal is reached or until 1 week before the start of each cohort study. Only the researcher conducting random assignments and the person who informs participants of their group allocation will be aware of the condition assignment.

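### The aim 1 model as most naturally read leaves out the three minimization factors, and the text does not clearly say which FACT-G result is primary

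*Protocol article*

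**What the plan says.** Under Randomization, the protocol article says: "Using minimization—a covariate adaptive randomization approach [26]—we will assign a participant to the intervention or control group". The algorithm is to "take into account participants’ age, stage of cancer, and time since completing treatment", and women go to the "Joy Luck Academy or control group at an approximate 1:1 ratio". HCA staff obtain the three covariates at screening.

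Under Deductive Data Analysis Plan, the mixed model is built from condition, time and their interaction: "the primary independent variables of interest will include the intervention condition (experimental vs control), time (postintervention and 1- and 4-month follow-ups". The aim 1 models take quality of life as the primary outcome and "other specified variables as secondary outcomes, controlling for the baseline outcome". The next sentence brings in the allocation factors: "In addition, results will be reported by controlling for important covariates used in the randomization". The three factors follow in parentheses, introduced by eg.

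The same section later exempts only the primary quality-of-life analysis from its warning that type I error is not controlled across the many tests.

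**The concern.** Minimization restricts chance imbalance on its factors. A model that leaves them out computes its standard error as if that imbalance were left to chance. Where the factors are prognostic, the standard error is too large, the interval too wide and the test conservative.

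The text also leaves open which model is primary. The multiplicity exemption needs one identified FACT-G analysis, but the wording yields two candidates: adjusted for baseline alone, and adjusted for baseline plus the allocation factors. The factors of the second are given only as examples, although the Randomization section names exactly three. If the choice is not fixed beforehand, it could follow the results.

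**Working it through.** **Inputs from the protocol article.** Power Analysis: d = 0.47, 146 women in total at 4 months, 80% power, α = .05, attrition 10 to 20%, recruitment goal 162 to 183. Deductive Data Analysis Plan: two-sided tests.

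**Inputs assumed.** R² is the share of 4-month FACT-G variance left after baseline FACT-G that the three factors explain. The documents give no value, so 0 to 10% is used. ρ, the baseline to follow-up correlation of FACT-G, is also not given; 0 (no baseline gain), 0.5 and 0.6 are used. d = 0.47 is taken to be on the raw standard deviation.

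**Step 1: the plan's own figures.** A two-sample t test with noncentral t gives 79.98% power at 72 per arm and 80.5% at 73 per arm, so the smallest total is 146, as stated. Attrition: 146/0.9 = 162.2 and 146/0.8 = 182.5, which matches 162 to 183. The sample size therefore takes no credit for any covariate.

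**Step 2: effect of leaving the factors out.** With 73 per arm, outcome SD 1 and the factors balanced:

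- Nominal SE without the factors: SE₀ = √(1−ρ²) × √(2/73), where √(2/73) = 0.1655.
- True SE: SE₁ = SE₀ × √(1−R²), so the overstatement is 1/√(1−R²) − 1.
- True type I error: 2[1 − Φ(1.96/√(1−R²))].
- Power without the factors: 1 − Φ((1.96·SE₀ − 0.47)/SE₁).
- Power with the factors: 1 − Φ(1.96 − 0.47/SE₁).

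With ρ = 0:

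| R² | SE too large by | Type I error | Power without | Power with | Loss (points) |
|---|---|---|---|---|---|
| 0 | 0% | 5.0% | 81.0% | 81.0% | 0 |
| 0.02 | 1.0% | 4.8% | 81.3% | 81.8% | 0.5 |
| 0.05 | 2.6% | 4.4% | 81.7% | 83.0% | 1.3 |
| 0.10 | 5.4% | 3.9% | 82.3% | 84.9% | 2.6 |

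**Step 3: allowing for the planned baseline adjustment.** The SE ratio and type I error do not depend on ρ. Power does:

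| ρ | R² | Power without | Power with | Loss (points) |
|---|---|---|---|---|
| 0.5 | 0.05 | 91.2% | 92.0% | 0.8 |
| 0.5 | 0.10 | 91.8% | 93.3% | 1.5 |
| 0.6 | 0.05 | 94.9% | 95.4% | 0.5 |
| 0.6 | 0.10 | 95.3% | 96.3% | 1.0 |

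**Step 4: does the formula survive imperfect balance?** Minimization was simulated with an assumed biased-coin probability of 0.8, N = 146, no baseline covariate and 3,000 runs per setting. At R² = 0.10 with no treatment effect, the model without the factors had a mean SE of 0.166 against an empirical SD of 0.156, with type I error 3.6%. With the factors the figures were 0.157, 0.156 and 4.7%. At d = 0.47, power was 81.4% without and 84.5% with. At R² = 0.05, power was 79.6% without and 80.8% with; the Monte Carlo standard error is √(0.8×0.2/3000) = 0.7 points, so the first figure cannot be told apart from 80%. At R² = 0 the two models agreed.

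**The case against.** The sentence on the allocation factors can also be read as adding them to the same model as the baseline outcome. On that reading the standard error problem disappears. This stands as a possible reading, but it is the less natural one, and a text open to both does not fix the primary model.

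A reader might infer that the primary standard error is in fact too large. The documents do not support that. It holds only if the three factors predict FACT-G beyond baseline FACT-G, and no such figure is given. Baseline adjustment may already absorb much of what they explain.

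A reader might also infer that imbalance on the factors cannot occur. The text says only that the algorithm takes them into account, and attrition of 10 to 20% comes before the 4-month analysis. The simulation shows that the perfect-balance formula is a fair approximation, but no more.

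Nor is the precision wasted, because adjusted results are to be reported, and showing both versions limits selective emphasis.

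Finally, the coding of the covariates is a detail that an article may leave to the full plan, and its absence is not part of this point.

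**Conclusion.** The point holds as a modest one. The trial allocates by three factors, and its analysis section, most naturally read, omits them from the aim 1 model and does not clearly name the primary FACT-G result.

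The statistical cost is conditional and small: a standard error 0 to 5.4% too large and a type I error of 5.0 to 3.9% for R² from 0 to 10%. The power loss is at most about 2.6 points, and about 0.5 to 1.5 points at R² of 5 to 10% once a baseline correlation of 0.5 to 0.6 is assumed. R² and ρ are assumptions.

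A stronger claim, that the planned test is invalid or the trial underpowered, would be wrong. With the factors balanced, leaving them out neither biases the estimate nor inflates type I error, and the stated 80% power is reached without them. The more lasting weakness is that two FACT-G results are foreseen and neither is clearly designated as the one that escapes the multiplicity caution.

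**What to change.** State in the Deductive Data Analysis Plan that the primary FACT-G model includes baseline FACT-G and all three minimization factors (age, cancer stage and time since completing treatment) as fixed covariates. Delete the eg, so that the list is closed. Label the model without the factors a sensitivity analysis.

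The wording change is a sentence or two. It needs no new data, because the values were to be obtained at screening, and no change in sample size. The Results section reports that data collection ended in February 2019, so the change should be a dated amendment made before outcomes are compared by arm. If that comparison has already been seen, the report should say so.

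There is a side benefit. The Missing Data section makes its missing-at-random assumption conditional on the variables in the model, so including the factors makes it easier to defend if dropout is related to them.

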### Objectives

We planned a randomized controlled trial (RCT) to test the health benefits of Joy Luck Academy and identify how and to whom the Joy Luck Academy is effective using a CBPR approach and mixed methods. This study is the first RCT to test a culturally and linguistically sensitive intervention designed to address the informational and emotional needs of Chinese American breast cancer survivors.

The primary aim of this study is to test the health benefits of a culturally sensitive social support program for Chinese American breast cancer survivors (aim 1). We hypothesize that the program will confer health benefits, as indicated by improvements in outcomes. The primary outcome is quality of life; the secondary outcomes are depressive symptoms, fatigue, positive affect, and perceived stress. We also expect that the intervention will normalize diurnal cortisol levels, an exploratory outcome. Secondary objectives include identifying the characteristics of individuals who benefit from the Joy Luck Academy (aim 2) and understanding the underlying mechanisms (aim 3). On the basis of the literature and our pilot study [15,17], we hypothesize that Joy Luck Academy will be more effective for women who lack psychosocial resources, specifically, those with low levels of social support, optimism, and perceived control over illness. We hypothesize that the Joy Luck Academy will increase relatedness need satisfaction and coping self-efficacy and decrease cancer-related perceived stigma, leading to health benefits (ie, mediators of the intervention effect).

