#### Exploratory Outcomes

Salivary cortisol levels will be assessed at baseline and immediately after the intervention. Participants will collect saliva 20 minutes after awakening and at 12 PM, 5 PM and 9 PM hours on 2 consecutive days so that both the mean level and slopes can be calculated [38]. Normal diurnal rhythms are expected to consistently demonstrate peak cortisol concentrations during awakening and decline thereafter [39]. Following established procedures [39,40], participants will be given detailed instructions on collecting saliva at home. Participants will be asked not to eat or drink anything, brush or floss their teeth, use mouthwash or lipstick, or smoke 30 minutes before collection. They will complete questions on comorbid conditions (such as autoimmune disorders) and medications (such as prednisone, dexamethasone, and other steroids), alcohol and caffeine intake, exercise level, and sleep quality, which influence cortisol levels. They will be given salivettes and then asked to chew a small cotton pad and spit it back into the tube of the salivette. Participants will be asked to mail their samples to the HCA office within 3 days after collection (salivary cortisol is stable at ambient temperature for 2-4 weeks) [40]. The samples will be stored in a freezer at −20°C until they are delivered in batches to a well-established independent laboratory for analysis; these procedures are routinely used [40].

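### Cortisol is to be tested as a pre-to-post change with no baseline adjustment stated, which on the usual reading is less precise than the method used for the questionnaire outcomes

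*Protocol article*

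**What the plan says.** All of this is in the Protocol article.

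- **Questionnaire outcomes.** Under Deductive Data Analysis Plan, the model has post-baseline times only: "time (postintervention and 1- and 4-month follow-ups), and the interaction between the intervention condition and time". Quality of life is the primary outcome, with "other specified variables as secondary outcomes, controlling for the baseline outcome".
- **Cortisol analysis.** The same section gives cortisol a separate rule: "We will analyze the impact of the intervention on cortisol by testing the change in diurnal profile from pre- to postintervention", by mixed-effects modeling. It adds: "Cortisol outcomes will be indicated by raw cortisol values, initial levels, slopes, and areas under the curve".
- **Cortisol visits.** Under Exploratory Outcomes: "Salivary cortisol levels will be assessed at baseline and immediately after the intervention". There are therefore two occasions, each with four samples a day on two days.
- **Status.** Under Objectives: "We also expect that the intervention will normalize diurnal cortisol levels, an exploratory outcome".

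The baseline-adjustment sentence names the primary and secondary outcomes. Cortisol is neither, so that sentence does not clearly cover it. The cortisol sentence does not say whether the arms may differ at baseline in the model.

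**The concern.** The trial collects a baseline cortisol profile and already uses the more efficient approach for its other aim 1 outcomes. A mixed model that takes both visits as outcome and tests condition by visit, with each arm's baseline mean estimated freely, gives baseline a fixed weight of 1. Baseline adjustment lets the data choose the weight. When the two visits are only moderately correlated, a weight of 1 is too large, and the standard error is larger than it needs to be.

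At stake is the precision of the cortisol estimates and of the 95% CIs that the article promises. The article itself lists influences on cortisol, such as sleep quality, exercise, caffeine and medication. Several of these can vary between visits, so a correlation near 1 should not be taken for granted.

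**Working it through.** **The plan's own figure.** The only sample size stated is for quality of life: "a total sample size of 146 women at the 4-month follow-up would yield 80% power to detect this treatment effect at α=.05" (Power Analysis, with d = 0.47). The normal approximation gives 2(1.96 + 0.84)²/0.47² ≈ 71, or 72 per arm with unrounded quantiles. The noncentral t gives 79.98% power at 72 per arm and 80.5% at 73, hence 146 in total. The figure reproduces, but it says nothing about cortisol. The article states no cortisol SD, effect size, correlation or evaluable number.

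**Inputs for the comparison.**
- Two occasions, baseline and postintervention (Exploratory Outcomes).
- Allocation of about 1:1 (Randomization).
- Assumed: equal SD σ at both occasions, and r over a range.

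**Step 1: per-woman variances.**
- Change score: σ² + σ² − 2rσ² = 2σ²(1 − r).
- Postintervention value adjusted for baseline: σ²(1 − r²).
- Ratio: 2(1 − r) / [(1 − r)(1 + r)] = 2/(1 + r), which exceeds 1 for every r below 1.

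The number of women per arm cancels. The share of effective sample lost is 1 − (1 + r)/2.

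**Step 2: results over the assumed range.**

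| r | change, 2(1 − r) | adjusted, 1 − r² | variance ratio | SE larger by | effective sample lost |
|---|---|---|---|---|---|
| 0.3 | 1.40 | 0.91 | 1.54 | 24% | 35% |
| 0.5 | 1.00 | 0.75 | 1.33 | 15% | 25% |
| 0.7 | 0.60 | 0.51 | 1.18 | 8% | 15% |
| 0.9 | 0.20 | 0.19 | 1.05 | 3% | 5% |

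**Step 3: does the mixed model behave this way?** Trials with 73 women per arm, both visits complete and a true difference of 0.47 SD were simulated and analyzed in four ways, 150 trials per value of r for the mixed models. The 0.47 only sets the scale; precision does not depend on it.

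- The mixed model with free baseline means reproduced the change-score difference (largest gap below 1e-14).
- The mixed model with a common baseline mean matched the precision of ANCOVA.
- The empirical SDs of the estimates were:

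| r | change score and free-baseline model | ANCOVA | common-baseline model |
|---|---|---|---|
| 0.3 | 0.198 | 0.169 | 0.169 |
| 0.5 | 0.155 | 0.137 | 0.138 |
| 0.7 | 0.122 | 0.112 | 0.111 |

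- All four estimators averaged between 0.459 and 0.480, close to the true 0.47. The difference is one of precision, not bias.

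**Step 4: unequal SDs.** With SD σ₀ before and σ₁ after, the change-score variance minus the adjusted variance is σ₀² − 2rσ₀σ₁ + r²σ₁² = (σ₀ − rσ₁)², which is never negative. The ratio moves away from 2/(1 + r), but apart from the small cost of estimating one slope, adjustment does not lose.

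**The case against.** The strongest reply is that the article does not fix the model being criticized. It says that change in the diurnal profile will be tested in a mixed model. It does not ask for change scores or say that the arms have free baseline means. A mixed model with a common baseline mean also tests change and has ANCOVA precision, so it fits the sentence. An article may leave such a detail for an exploratory biomarker to a fuller document, and the sources it cites for the cortisol methods are not at hand. There is also a natural reason for different wording: cortisol has two visits where the questionnaires have four, and the hypothesis concerns the shape of a daily profile.

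This stands in part. The loss is likely on the ordinary reading, but not certain. What remains is that the article states a separate rule for cortisol, describes it as change, and states neither safeguard, although a more precise method is available from data already collected.

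A reader might go further in four ways that the document does not support:

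- *That baseline is thrown away.* A change score uses baseline, with a fixed weight instead of an estimated one.
- *That the article defines two different effects, or that the cortisol result is biased.* Under randomization both contrasts target the same between-arm difference. Chance baseline imbalance is the source of the extra variance, not a second harm.
- *That a specific amount of power is lost.* This would mean borrowing the pilot effect of 0.47 and 73 per arm, which belong to quality of life at 4 months. The article gives no cortisol counterpart.
- *That the trial's conclusions are at risk.* Cortisol is exploratory and unpowered, and the article already says that findings outside the primary analysis will be interpreted with caution.

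**Conclusion.** The point holds as a low-severity, free improvement. As worded, and on the usual reading, the cortisol comparison is a difference in change scores. It is unbiased under randomization, with variance 2/(1 + r) times that of the baseline-adjusted comparison: 1.54 at r = 0.3, falling to 1.05 at r = 0.9.

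The size rests on equal SDs, complete data at both visits, and values of r that are assumed because the article gives none. If r is high, little is lost. If the intended model already has a common baseline mean, nothing is lost and only the wording needs completing.

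One further assumption applies to every version of the analysis: baseline saliva must be unaffected by knowledge of allocation. Randomization is scheduled to begin four weeks before orientation, and the baseline questionnaires are completed at orientation. The article does not say whether baseline saliva is collected before women learn their group.

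The primary FACT-G analysis and the secondary outcomes are already adjusted for baseline and are not affected.

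**What to change.** Replace the cortisol sentence with two statements:

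1. Each postintervention cortisol summary (initial level, slope, area under the curve) is compared between arms, adjusted for the woman's own baseline value of the same summary.
2. The mixed model for raw values keeps both visits as outcome but constrains the arms to a common baseline diurnal profile, with no condition or condition-by-time-of-day terms at baseline. It tests the condition-by-postintervention terms, including their interaction with time of day.

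The cost is a sentence or two and a different model statement. No new data or measurements are needed. The common-baseline constraint follows from randomization, provided that baseline saliva is not influenced by allocation; the authors should confirm this in the same place. The article reports data collection as complete with results still to come, so the choice should be recorded before the cortisol data are compared by arm.
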